### Sample size

Previous NHS GG&C studies,^10 21^ combined with internal audit data (showing that 80% of patients have direct or daily smartphone, tablet or web access), indicate that recruitment of 400 participants across a 12-month period is feasible, and likely to provide adequate data to conduct meaningful primary and secondary endpoint analyses.

An improvement in admission-free survival, with reduction in admissions by one per patient per year is projected, if support for provision of evidence-based COPD care is achieved by the service model. As the feasibility of an end-to-end digitalised service model for COPD has not yet been tested, and the service components will be adapted during the study, sample size power calculations and randomisation are not yet appropriate.

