### Machine learning analysis and predictive modelling

These analyses will be conducted post hoc, using the clinical data obtained from the RECEIVER trial COPD platforms, alongside EHR data in historical and contemporary control patients from NHS GG&C SafeHaven. The anticipation is that following analysis of the study data, we will be able to judge the feasibility and accuracy of using predictive model outputs at a service or individual patient level. This may lead to the subsequent development and evaluation of artificial intelligence(AI)-based clinical decision support tools. Relevant clinical investigation/medical device trial(s) of these would be proposed and designed. The data from the RECEIVER trial would not be used directly to support clinical validation of any subsequently developed medical device.

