### Secondary endpoint measures

Clinical events, hospital occupied bed days, treatment uptake, NIV usage and therapy, incidences of supported self-management and the impact of demographics on these will be captured within the digital service platform with data from weekly SafeHaven export, Trakcare real-time episode data feed and platform tracking analytics.

The process evaluation metrics for the digital service model will be captured by platform tracking analytics, project delivery process documentation and supplementary user experience research conducted as part of the digital service project delivery.

Machine learning-supported analysis of study dataset will be conducted post hoc.

Patient-centred outcomes will be captured within RECEIVER patient portal.

Qualitative user experience research will be undertaken with a subgroup of participants to inform implementation strategy and will be presented as a descriptive summary. A sample of convenience will be taken from within the RECEIVER cohort. Semistructured interviews will be conducted, and thematic analysis will be performed. Interview transcripts will be coded, and the codes used to generate themes. Discussion of the themes within the research team will be conducted to ensure agreement and add rigour.

Cost analysis will be based on audited accounts for the RECEIVER innovation project delivery, combined with standard NHS tariffs, NHS Scotland medical/agenda for change salary scales and indirect costs from standard burden of COPD cost projections.

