## Statistics and data analysis

Secondary outcomes in the RECEIVER observational cohort will be compared with matched retrospective data from de-identified linked datasets of historical control and contemporary control high-risk patients with COPD. These will comprise of patients identified from coding and admission data as having had severe exacerbation of COPD between 1 January 2010 and 30 April 2019 (historical cohort) and between 1 July 2019 and 30 June 2020, excluding participants enrolled in the RECEIVER Study (contemporary control). The historical control dataset will contribute to machine learning models development. Secondary outcome analysis will be separately compared between the RECEIVER cohort, historical cohort and contemporary control cohort. This component of the study is also separately registered with dataset access approval from NHS GG&C SafeHaven LPAC.

The clinical endpoint data will be reported as a proportion and 95% CI for that outcome, calculated by Kaplan-Meier method. Demographic data will be presented as mean and SDs, or medians and IQRs as appropriate. Correlation, t-test, analysis of variance and effect size analyses will be used as appropriate for secondary endpoint analysis, comparing results of clinical endpoint and patient-centred outcomes with NIV therapy and supported self-management parameters.

Machine learning ensemble methods will be used to develop binary classification problems for patient risk. Precision, recall, accuracy and C-statistics of the receiver operating characteristic curve will be used to evaluate model performance.

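### None of the named performance measures assesses calibration, although model outputs are to be judged for use in single patients or across the service

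*Protocol article*

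**What the plan says.** Under Statistics and data analysis, the protocol article sets the modelling task: "Machine learning ensemble methods will be used to develop binary classification problems for patient risk". The next sentence names the measures: "Precision, recall, accuracy and C-statistics of the receiver operating characteristic curve will be used to evaluate model performance". The same section says that the historical control data, from 1 January 2010 to 30 April 2019, will contribute to building the models.

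The purpose is given under Machine learning analysis and predictive modelling, where the investigators expect that "we will be able to judge the feasibility and accuracy of using predictive model outputs at a service or individual patient level". Decision support tools are mentioned there as a possible later step.

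The article also limits the weight of this work. Secondary endpoint measures says that "Machine learning-supported analysis of study dataset will be conducted post hoc", and Table 1 labels these analyses exploratory. The machine learning section adds: "The data from the RECEIVER trial would not be used directly to support clinical validation of any subsequently developed medical device".

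No calibration measure (plot, intercept, slope or Brier score) is named anywhere in the article. It gives no prediction window and no event rate for one.

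**The concern.** A model can rank patients well and still give wrong risks. The C-statistic depends only on the ranking. Precision, recall and accuracy depend only on which side of a threshold each prediction falls. Using an output for one patient, or adding risks up to plan a service, needs the numbers themselves to be right. The four named measures do not test that.

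Miscalibration is plausible here on the protocol's own facts. Older data feed the models. Sample size projects one admission fewer per patient per year if the service succeeds. The September 2020 amendment describes a pandemic that changed the setting of care. Each could move event rates between development data and trial-era data.

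A smaller matter is that accuracy is hard to read without the event rate, because its value for a model with no skill depends entirely on that rate.

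At stake is whether a model is judged ready for further development on figures that do not cover the use in view.

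**Working it through.** The protocol states no figure on this point, so there is none to reproduce.

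**Inputs.** From the protocol: the four measures, the binary classification task and the stated purpose. Assumed: event rates, the spread of risks, a threshold of 0.5 and the form of the distortion.

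**Step 1: what the measures can see.** Let L be the true logit of a patient's risk. Replacing L by 2L keeps the ranking, so the C-statistic cannot change. It also keeps the sign of L, so at a threshold of 0.5 every classification stays the same, and with it precision, recall and accuracy. The risks do change, because doubling the logit squares the odds. A true risk of 20% has odds 0.20/0.80 = 0.25. Squared, this is 0.0625, a stated risk of 0.0625/1.0625 = 5.9%.

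**Step 2: size in simulation.** L was drawn as a + 1.1 × Z, with Z standard normal and a = -3.4, -1.6 or 0, for 400,000 simulated patients per setting.

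| Event rate | Predictions | Mean predicted risk | C-statistic | Accuracy | Recall | Precision | Brier |
|---|---|---|---|---|---|---|---|
| 5.2% | correct | 5.2% | 0.7715 | 0.948 | 0.012 | 0.570 | 0.0459 |
| 5.2% | logit doubled | 0.9% | 0.7715 | 0.948 | 0.012 | 0.570 | 0.0490 |
| 21.3% | correct | 21.3% | 0.7610 | 0.803 | 0.210 | 0.613 | 0.1411 |
| 21.3% | logit doubled | 12.8% | 0.7610 | 0.803 | 0.210 | 0.613 | 0.1524 |
| 21.3% | logit + 1.5 | 48.0% | 0.7610 | 0.647 | 0.760 | 0.350 | 0.2195 |
| 50.2% | correct | 50.1% | 0.7580 | 0.690 | 0.690 | 0.691 | 0.1999 |
| 50.2% | logit doubled | 50.1% | 0.7580 | 0.690 | 0.690 | 0.691 | 0.2122 |

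Mean predicted risk is too low by a factor of 21.3/12.8 = 1.7 in one setting and 5.2/0.9 = 5.8 in another, with all four measures unmoved.

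**Step 3: limits of that result.** A uniform shift of the logit by 1.5 does move precision, recall and accuracy at a fixed threshold, so not every miscalibration is invisible. The movement does not show its cause, however, and it disappears if the threshold is moved by the same amount.

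**Step 4: what calibration measures show.** Regress the outcome on the predicted logit. For doubled logits, L = 0.5 × (2L), so the slope is 0.5 and the intercept 0. For the shift, L = (L + 1.5) - 1.5, so the slope is 1 and the intercept -1.5. At an event rate of 50.2% the mean prediction is unaffected by doubling, so comparing means alone would miss the fault. The slope shows it.

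**Step 5: accuracy and the event rate.** A model that never predicts an event has accuracy 1 - p, where p is the event rate. Take p = 1 - exp(-rate × days/365) and an assumed rate of 2 events a year:
- 7 days: p = 3.8%, accuracy 96%
- 14 days: p = 7.4%, accuracy 93% (96% to 89% at rates of 1 to 3 a year)
- 30 days: p = 15.2%, accuracy 85%
- 12 months: p = 1 - exp(-2) = 86%, accuracy 14%

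The useful reference is therefore the larger of p and 1 - p. In the table, at an event rate of 5.2%, the correct model's accuracy of 0.948 equals 1 - 0.052 = 0.948. Accuracy alone cannot separate it from a model that never predicts an event.

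**The case against.** The measures are conventional for binary classification. The work is exploratory and post hoc, partly meant to rank data inputs for a later study, and discrimination serves that aim. The article bars direct use of these data for validating a device. It does not say that the list is exhaustive, and a full protocol or analysis plan may add calibration.

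Much of this stands, and it keeps the weight low. It does not remove the mismatch. The article names a list and states an individual-level use that the list cannot assess. Nor does the binary task make calibration irrelevant: an ROC curve needs a graded score, so there are graded outputs to examine.

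A reader might also infer that the list favours a model that never predicts an exacerbation. It does not. Such a model has recall 0, undefined precision and a C-statistic of 0.5, so three of the four measures expose it. Only accuracy read alone flatters it, and only when events are uncommon. Step 5 shows that this depends wholly on a window and a rate that the protocol does not give.

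**Conclusion.** The point holds as a minor, specific improvement. The four named measures cannot show whether predicted risks are numerically right, and the stated purpose needs that. In the simulated settings, mean predicted risk could be wrong by a factor of up to about 6 with all four measures unchanged. That size rests on assumed event rates, an assumed spread of risks, a 0.5 threshold and a chosen distortion. How far event rates will actually shift cannot be derived from the document.

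A reader might infer that a decision to start a device trial would rest on these figures. The text says only that the work may lead to later tools, with separate trials to be designed. The effect is on the judgement of feasibility for that later work. The primary endpoint, the proportion of participants using the service, is untouched.

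**What to change.** Keep the four measures. Add a calibration plot with calibration intercept and slope, and the Brier score, all computed from the same predictions. The plot, intercept and slope matter most: the Brier score mixes calibration with discrimination and moved little in the rarest-event setting (0.0459 to 0.0490). Report accuracy beside the event rate, with the accuracy of always predicting the commoner class as the reference.

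The cost is a few more lines of analysis and no new data. The downside is that reported performance may look less favourable.

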## RECEIVER trial qualitative substudy: protocol addition and amendment September 2020

Following the outbreak of the COVID-19 pandemic, the digital service model established in the RECEIVER trial was adopted for routine clinical care in NHS GG&C. This was to mitigate for the anticipated COVID-19 impacts on routine COPD care, with concern about increased winter admission risks and continued requirement to maintain social distancing with vulnerable/shielding patients. Process for invitation and remote enrolment in the COPD digital service, via support website, has been established. People with COPD are enrolled following clinician referral or via invitations sent by Short Message Service (SMS) and letters to known patient cohorts.

Patient utilisation, clinical and service outcomes in this scale-up cohort will be evaluated in parallel with the data from the RECEIVER trial. These analyses will be conducted on de-identified data derived from NHS GG&C SafeHaven. There is separate ethics approval and protocol for these analyses.

It is relevant to gather user experience of the remote invitation and enrolment process to the digital service model and determine whether there are different experiences based on the recruitment source (via clinical trial, via invitation and website registration, via clinician referral). A sample of convenience of people who have enrolled in the COPD digital service via this scale-up service model will be established by the clinical team. They will be approached by the clinical team via the digital service messaging interface. People expressing an interest in undertaking semistructured interviews about their service experience will be sent a RECEIVER substudy patient information sheet and consent form. These people would then be contacted by one of the study investigators with the consent form discussed and completed by telephone, avoiding COVID-19 context risk of face-to-face contact for vulnerable individuals. The consent form with investigator signature would be mailed to the participant. Semistructured interviews would then be scheduled and conducted by telephone or video call, using NHS GG&C Attend Anywhere platform.

## Assessment of safety

The ‘RECEIVER’ digital service model is supporting rather than varying routine clinical care in people with COPD. Adverse device events and serious adverse events (ADEs and SAEs) will be captured within patient portal (eg, PRO question: have you had any hospital admissions?) and within COPD platform (by Trakcare-derived clinical events) and provided as a summary report.

Where an SAE requires recording, full details including the nature of the event, start and stop dates, severity, relationship to research product and/or trial procedures, and the outcome of the event will be recorded in the participant’s medical notes and CRFs. These events will be monitored and followed up until satisfactory resolution and stabilisation.

Each SAE will be assessed to determine if related to the research procedures and expectedness where the event is related by the following definitions:

Related: that is, it resulted from administration of study medicines or any of the research procedures.Expectedness of SAEs: is against the research procedure events listed in study protocol as an expected occurrence.

### Expected adverse events

In general, there is little additional risk to participants taking part in the study. However, the study aims to digitalise existing reporting pathways and therefore the potential exists for failures to occur within the software used. Expected adverse events related to use of RECEIVER platform are as follows:

Data connectivity issues: there may be issues with transfer of data from the participant to RECEIVER platform. Where these data relate to symptom diaries or Fitbit wearable data, there would be no impact on clinical care should the loss of data be temporary. However, in the event the data were permanently lost, this may impact on patient care.Messaging: there is a potential for messages sent from the participant to study staff (and vice versa) via the RECEIVER platform to be missed. There is also the potential for these messages to be confusing to the participant.Identity: there is the potential for data for one participant to be allocated incorrectly to another participant due to errors within the RECEIVER platform software.

Adverse effects unrelated to the use of the RECEIVER platform are not considered reportable to the sponsor.

Exacerbation of COPD resulting in hospitalisation and potentially death is expected within the study population. In addition, people with COPD may have other comorbid conditions. Events related to these conditions that meet the criteria of an SAE would also be considered expected. SAEs related to the participants’ underlying medical condition(s) that are not causally related to the RECEIVER platform are not reportable to the sponsor.

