### Safety reporting to sponsor

The following events are reportable to the sponsor:

Any SAE that is causally related to the use of RECEIVER platform (serious adverse device effect—SADE) regardless of expectedness.Any SAE that is related to the individual’s participation within the trial that is both related and unexpected but is not related to the use of the RECEIVER platform (related and unexpected SAEs—RUSAEs).

Study-related unexpected SAE must be reported to the Pharmacovigilance (PV) office immediately (within 24 hours). The SAE form should be completed and signed by appropriately delegated staff. If necessary, a verbal report can be given by contacting the PV office. This must be followed up as soon as possible with a signed written (or electronic) report. If all of the required information is not available at the time of initial reporting, the PI (or designee) must ensure that any missing information is forwarded to the PV office as soon as this becomes available. The report should indicate that this information is follow-up information for a previously reported event.

The PV office will report all RUSAEs and unexpected SADEs (USADEs) to the ethics committee within 15 days of the PV office becoming aware of the event, via the ‘report of SAE form’ for non-Clinical Trial of an Investigational Medicinal Products (non-CTIMPs) published on the Health Research Authority website.

RUSAEs and USADEs will also be considered individually by project steering group. Where appropriate, modifications (eg, additional patient alert notifications, additional clinical decision support notifications) to the RECEIVER platform will be made, in discussion with ethics committee and supported by protocol amendment.

Annual progress/safety report will be provided by the PI to the Research Ethics Committee(REC) and Research and Development (R&D) department.

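### The safety rules conflict on participation-related, unexpected SAEs not due to the platform, and leave open whether serious harm from a listed platform failure counts as expected

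*Protocol article*

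**What the plan says.** Three adjoining parts of the protocol article set the rules.

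- **Assessment of safety** says how expectedness is decided: "Expectedness of SAEs: is against the research procedure events listed in study protocol as an expected occurrence". It also provides for adverse device events and SAEs to be captured and summarised.
- **Expected adverse events** lists three kinds of platform failure: data connectivity, messaging and identity. On messaging it says that "there is a potential for messages sent from the participant to study staff (and vice versa) via the RECEIVER platform to be missed". It then states: "Adverse effects unrelated to the use of the RECEIVER platform are not considered reportable to the sponsor". A later paragraph calls COPD exacerbation leading to admission, and possibly death, expected in this population. That paragraph excludes SAEs arising from underlying conditions "that are not causally related to the RECEIVER platform are not reportable to the sponsor".
- **Safety reporting to sponsor** names two reportable classes. The first is "Any SAE that is causally related to the use of RECEIVER platform (serious adverse device effect—SADE) regardless of expectedness". The second is an SAE linked to taking part in the trial that "is both related and unexpected but is not related to the use of the RECEIVER platform" (RUSAE). The 24-hour report to the pharmacovigilance office is stated for study-related SAEs that are unexpected. The 15-day report to the ethics committee covers RUSAEs and unexpected SADEs (USADEs). On internal review the section says: "RUSAEs and USADEs will also be considered individually by project steering group". Platform modifications are attached to that step. An annual progress and safety report goes to the ethics committee and the R&D department.

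**The concern.** There are two separate problems.

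First, an investigator with an unexpected SAE caused by a trial procedure outside the platform finds two instructions. One section says the event is not reportable to the sponsor; the next says it is. An investigator who follows the first would not report an event that the second requires. Because the pharmacovigilance office makes the ethics report once it becomes aware of an event, an unreported event could also miss the ethics committee and the steering group.

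Second, the only platform risks that the protocol lists are placed under the heading of expected events, and the faster and closer forms of review are kept for unexpected ones. If a serious harm takes its classification from the failure that caused it, it misses the step at which the steering group can decide to change the platform. The modifications given as examples there include extra patient alerts, which would be a natural response to missed messages.

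**Working it through.** No sample size, error rate or event count is involved, so the check is a cross-tabulation of the reporting rules. Each type of SAE is set against each route stated in the article.

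| Type of SAE | Sponsor | 24-hour rule as worded | Ethics report within 15 days | Individual steering-group consideration |
|---|---|---|---|---|
| (a) Platform-related, unexpected (USADE) | Yes | Yes | Yes | Yes |
| (b) Platform-related, classed as expected | Yes | Not stated | No | No |
| (c) Participation-related, unexpected, not platform-related (RUSAE) | **No** under Expected adverse events; **yes** under Safety reporting to sponsor | Yes | Yes | Yes |
| (d) Due to underlying disease, not platform-related | No | No | No | No |

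**Row (c): the contradiction.** The exclusion quoted above has no exception. The RUSAE class is defined as "both related and unexpected but is not related to the use of the RECEIVER platform", so every RUSAE falls within the words of the exclusion. The class is not empty in principle: the physiology substudy adds oscillometry, parasternal EMG and home air pollution monitoring, which are research measurements outside the platform.

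**Row (d): no contradiction.** The separate sentence on underlying conditions agrees with the reporting section. Disease-related SAEs are non-reportable under both.

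**Row (b): how a serious harm could land there.**

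1. Expectedness is judged against events listed in the protocol.
2. The list names connectivity, messaging and identity failures.
3. The same section calls COPD admission or death expected in the population.
4. Take a missed message followed by an admitted exacerbation that is judged to be caused by the missed message. The cause is on the list, and the consequence is described as expected. An assessor can therefore class the event as an expected SADE.
5. The event then goes to the sponsor, because SADEs are reportable whatever their expectedness, and it could appear in the annual report. It meets neither the condition for the 15-day ethics report nor that for individual steering-group consideration, and the 24-hour sentence does not name it.

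If the assessor instead holds that the list covers only the software fault, the same event moves to row (a) and gets all the routes. The text does not settle which row applies.

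**The case against.** The case on the other side has real content.

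- **The contradiction is narrow.** The excluding sentence speaks of adverse effects rather than SAEs and sits under a heading about expected events. The reporting section is the operative list and names RUSAEs expressly. SAEs from the substudy measurements may well be rare. The narrowness stands, and the point is confined to that class. Reading the sentence as covering only non-serious or disease-related effects would remove the conflict, but the article does not say so. Disease-related SAEs also have their own exclusion a few lines later.
- **The list names faults, not clinical harm.** An admission or death caused by the platform is not on the list of platform failures, and the remark about COPD admission and death sits in a paragraph about underlying disease. On that reading, serious harm from a missed message is an unexpected SADE and gets every safeguard. This reading is tenable. It shows that the text is ambiguous, not that it is settled.
- **A missing deadline for expected SADEs may be in the full protocol.** That is fair for a condensed article. The point here is only that the 24-hour sentence, as worded, covers unexpected events; the missing deadline is not raised as a fault in itself.
- **Limiting expedited ethics reporting to unexpected events is a coherent choice.** Agreed. The point does not challenge that choice. It concerns what counts as expected.

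A reader might infer that platform harms are kept out of ethics and steering-group review altogether. The documents do not support that: SADEs reach the sponsor regardless of expectedness, an annual report goes to the ethics committee, and adverse device events and SAEs are summarised. The steering group also considers service iterations every three months, although the article does not describe this as a review of safety events. Nor do the documents show that the listed failures are the harms most likely to occur, since no frequencies are given.

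**Conclusion.** The point holds in two limited parts.

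1. There is a direct contradiction on sponsor reporting for one of the four types of SAE set out above, the RUSAEs. It rests on the plain words of two adjoining sections and needs no assumption beyond reading adverse effects to include serious ones.
2. There is an ambiguity over expectedness. A serious harm caused by any of the three listed platform failures can be classed as expected. It would then fall outside the 24-hour rule as worded, the 15-day ethics report and individual steering-group consideration. This depends on the assessor taking the listed fault, or the listed COPD outcome, as deciding expectedness. It cannot be said flatly that such an event triggers none of these safeguards, because the other reading is open.

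The number of events affected cannot be estimated from the article. No endpoint or analysis changes. The point matters for participant safety and for consistent reporting, and it should be corrected because the remedy is so small.

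**What to change.** Two wording changes are enough.

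- In Expected adverse events, except RUSAEs from the sentence that makes effects unrelated to the platform non-reportable, so that it agrees with Safety reporting to sponsor.
- In the same section, state that the list of expected platform events covers the technical fault only. An SAE causally related to a platform failure is then handled as an unexpected SADE under the routes that already exist.

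No new reporting route is needed. The cost is possibly a minor amendment, and a few more reports to the pharmacovigilance office, the ethics committee and the steering group.
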